**Figure 6 figure6:**
[figure not shown]
Workflow process map. AF: atrial fibrillation; APP: advanced practice provider; BMP: basic metabolic panel; CBC: complete blood count; CMP: comprehensive metabolic panel; ED: emergency department; HF: heart failure; IV: intravenous; LE: lower extremity; MCI: multivariate change index; NT-proBNP: N-terminal pro–B-type natriuretic peptide; SOB: shortness of breath.

If there is a tachypnea or tachycardia event, the HHN will evaluate whether this is the first time such an event has occurred or whether there is any increasing occurrence of these events. If so, the HHN will call and assess the patient and complete the structured note. Recommendations for management include calling the APP and HF specialist, considering conducting basic laboratory tests, and considering an oral diuretic escalation. If the APP or HF specialist is contacted, they will review the vendor platform and have a telephone visit with the patient. On the basis of their clinical assessment, they will consider an oral diuretic dose increase and determine whether the patient needs to be seen for an in-person visit. The telephone visit assessment will be sent to the HHN.

If the patient’s diuretic dose has been escalated or if they are on IV diuretics, the patient’s laboratory test results will be checked on the third day of taking an escalated dose. If a patient on an already escalated diuretic dose has an event notification, new or worsening symptoms, or increased weight gain, the HHN will call the APP or HF specialist for further guidance. Recommended interventions include a home evaluation, an urgent HF clinic evaluation, or an IV diuretic at home. A patient’s escalated diuretic dose will be de-escalated once their symptoms have resolved or their weight has reverted to their dry weight (normal weight without any extra fluid in the body).

If a patient has >1 alert, the pathway for the alert deemed more severe will be followed. The severity of alerts in order from more severe to less severe are as follows: any new or worsening red zone symptoms, any new or worsening yellow zone symptoms, weight gain of ≥5 lb (≥2.3 kg), an MCI alert, an atrial fibrillation with rapid ventricular response alert, and a tachypnea or tachycardia alert. For example, if the patient has a new red zone symptom and an MCI alert, the pathway for the red zone alert will be followed. The more severe alerts are depicted higher up on the workflow shown in Figure 6.

When the HHN escalates care to the APP or HF specialist, suggested management and treatment plans will be available to the clinical care team, but nuanced clinical judgment is ultimately left to the provider in managing these patients with complex medical needs.

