### Workflow and Clinical Management

The workflow process map is shown in Figure 6. The HHN reviews the web-based platform daily for any clinical event–driven notifications. The daily ePRO, which includes the patient’s daily weight and whether they are having symptoms related to HF, is also reviewed [44,45]. If a patient reports any symptoms on a particular day, the patient survey will also ask whether the symptoms are getting better, worse, or the same the following day.

If there are any red zone symptoms reported, which include symptoms of chest pain, shortness of breath at rest, wheezing at rest, swelling of the hands or face, confusion, anxiety, or feeling as though they must sit up to breathe, the HHN will call the HF specialist or send the patient to the emergency department (ED).

If there are any new or worsening symptoms of shortness of breath, orthopnea, or lower extremity edema (yellow zone symptoms), the HHN will call the patient and complete the structured EHR documentation note. The HHN documentation note provides automated management recommendations based on the information filled out in the note. In the case of a note stemming from new or worsening yellow zone symptoms, recommendations include increasing the oral diuretic dose and considering an in-house evaluation. The note will be forwarded to the APP pool and the patient’s HF specialist. The APP in turn will schedule a telephone visit with the patient and determine whether the patient needs home IV diuresis. If so, they will provide a prescription for this, and home health services will start IV diuretics at home. The HF attending physician and the HHN will be alerted of this plan.

If the patient has a weight gain of ≥5 lb (≥2.3 kg) compared with their baseline weight, the HHN will call the patient and complete the structured documentation note. Potential automated recommendations to consider include escalating the oral diuretic dose. The HHN will route the note to both the HF APPs and attending physician. The APP will follow up with the patient and schedule a telephone visit with the patient. The APP will assess whether the patient needs home IV diuresis, and if so, they will prescribe it. This plan will be communicated to the HF attending physician and the HHN.

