If there is an MCI event, the HHN will call the patient and complete the structured note. Management recommendations include sending a visiting HHN to draw a complete blood count, a complete metabolic panel, and an N-terminal pro–B-type natriuretic peptide, as well as possible oral diuretic dose escalation. The HHN will also call the APP and route their note to the APP and HF attending physician. The APP will schedule a telephone visit with the patient and follow up on any laboratory test results. On the basis of their telephone visit, the patient’s ePROs, and any laboratory test results obtained, the APP will form a clinical assessment regarding the patient. On the basis of this assessment the APP will determine whether any of the following is indicated: an escalation of the oral diuretic dose, an urgent in-person clinic visit, and whether the HF attending physician needs to be alerted.

If there is an atrial fibrillation with rapid ventricular response event, the HHN will call the patient and complete the structured EHR note, call the APP or HF specialist, and route the note to the APP pool and HF specialist, or send the patient to the emergency room. If the APP is alerted to an atrial fibrillation with rapid ventricular response event, they will review the vendor platform to assess the event and the patient’s vital signs obtained from the biosensor. They will also schedule an urgent telephone or video visit with the patient to further assess them. The APP will determine whether the patient needs to be sent to the ED or whether the patient can be safely managed at home. The APP will also discuss their assessment with the HF attending physician to ensure that they agree with the plan.

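### When atrial fibrillation with rapid ventricular response coincides with yellow zone symptoms, weight gain or an MCI alert, the ranking rule selects a pathway that omits the nurse's emergency room option and does not assure the APP's urgent steps

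*Protocol article*

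**What the plan says.** All of this is in the protocol article, Methods, Workflow and Clinical Management, unless noted.

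- **Rule for coinciding alerts:** "If a patient has >1 alert, the pathway for the alert deemed more severe will be followed". The worked example pairs a red zone symptom with an MCI alert and follows the red zone pathway.
- **Ranking:** red zone symptoms, yellow zone symptoms and weight gain come first, then "an MCI alert, an atrial fibrillation with rapid ventricular response alert, and a tachypnea or tachycardia alert". AF with RVR is therefore fifth of six.
- **AF with RVR pathway, nurse:** telephone the patient, fill in the structured note and contact the APP or HF specialist by call. The instruction ends with these words: "and route the note to the APP pool and HF specialist, or send the patient to the emergency room".
- **AF with RVR pathway, APP:** the steps open with a condition, "If the APP is alerted to an atrial fibrillation with rapid ventricular response event". The APP then reviews the platform, arranges an urgent remote visit, chooses between the ED and home management, and discusses this with the attending physician.
- **Yellow zone pathway:** "The note will be forwarded to the APP pool" and to the HF specialist. The APP follows with a telephone visit and a decision on home IV diuresis.
- **Weight gain pathway:** "The HHN will route the note to both the HF APPs and attending physician". The APP's follow-up is the same.
- **MCI pathway:** "The HHN will also call the APP and route their note to the APP and HF attending physician". The APP's options include "an urgent in-person clinic visit".
- **Notification in general** (Device and Notification Mechanisms): once the nurse's escalation criteria are met, who is notified turns on how acute the event is, what kind it is, and who is on call.

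**The concern.** The order of severity does not match the urgency of the responses. Apart from the red zone, AF with RVR has the most urgent written response, yet three alerts with less urgent responses outrank it. Read as written, the rule means that a second sign of deterioration can make the nurse's written response to the arrhythmia less urgent than it would be for the arrhythmia alone.

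Written steps carry weight in this study. The account of phase 1 in the Results says that only the MCI alert then had tailored recommendations, that staff had difficulty deciding how to act on other alerts, and that APPs were at times unsure how to respond. Tailored pathways were added for that reason, and the ranking rule sets the AF with RVR one aside in these pairings. The phase 1 experience concerns the earlier workflow and does not mention coinciding alerts, so it shows why written guidance matters here, not that this problem has occurred.

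What is at stake is patient safety. No sample size, endpoint or analysis is affected.

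**Working it through.** No figure in the article needs reproducing. The check compares the pathways and then applies the rule.

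**1. The pathways side by side, as described in the text**

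| Alert, in ranked order | Nurse may send to emergency care | Nurse's contact with APP or HF specialist | Most urgent step listed for the APP |
|---|---|---|---|
| Red zone | Yes | Call to HF specialist (alternative to ED) | None described |
| Yellow zone | Not listed | Note forwarded | Telephone visit; home IV diuresis decision |
| Weight gain | Not listed | Note routed | Telephone visit; home IV diuresis decision |
| MCI | Not listed | Call to APP, plus note | Telephone visit; urgent clinic visit as an option |
| AF with RVR | Yes, as an alternative | Call, plus note | Urgent remote visit; ED-or-home decision |
| Tachypnea or tachycardia | Not listed | Call recommended | Telephone visit; in-person visit considered |

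**2. Which pairings are affected**

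Six alert classes give 6 − 1 = 5 pairings that contain AF with RVR.

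- With tachypnea or tachycardia, AF with RVR ranks higher and its own pathway is followed.
- With red zone symptoms, the red zone pathway is followed, and it lists the ED.
- That leaves 5 − 2 = 3: yellow zone, weight gain and MCI.

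**3. What changes for the nurse in those three**

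- *Yellow zone or weight gain:* the patient call and the note remain. The emergency room option is no longer listed, and the call to the APP or HF specialist becomes a forwarded or routed note.
- *MCI:* the patient call, the call to the APP and the note all remain. Only the emergency room branch goes.
- *Diuretic dose already escalated:* a separate rule has the nurse call the APP or HF specialist about any event notification, new or worsening symptom, or further weight gain. That restores the call in the first two pairings. The interventions it recommends include an urgent HF clinic evaluation but not the ED.

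**4. What changes for the APP**

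The APP receives a note or call in all three pairings, prompted by the higher-ranked alert. The platform review, urgent visit and ED-or-home decision apply if the APP is alerted to the AF with RVR event. The general notification sentence makes that possible, because acuity and event type are among its criteria. No sentence says the lower-ranked event is passed on, so these steps are conditional, not lost.

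**5. Can the alerts coincide?**

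One MCI notification is for elevated heart rate (Device and Notification Mechanisms), and the nurse reviews the platform daily, so same-day overlap is plausible. The article gives no frequency.

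**The case against.** The strongest case on the other side has five parts.

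- **The rule does not say that only one pathway is followed, and the nurse recommendations are open lists.** An item missing from such a list is not prohibited. This stands as far as it goes. But the worked example shows one pathway being selected, and nothing says the steps of the lower-ranked alert are added.
- **Figure 6 and the structured note are not shown, and the note drives the cascade.** They may handle coinciding alerts better than the text does. This is a real limit on certainty. The text does say that Figure 6 places more severe alerts higher, which agrees with the ranking.
- **Provider judgement governs.** It does, but the sentence reserving it applies once the nurse has escalated to the APP or HF specialist. It tempers the consequence without putting the nurse's emergency room option back into the pathway.
- **Other protection exists.** Chest pain, shortness of breath at rest and confusion are red zone symptoms and take priority. The nurse telephones the patient in all three pairings, and an APP is reached. This stands and keeps the point modest, especially for MCI, where one optional branch is the only difference for the nurse.
- **The order is the clinical team's choice.** That stands too, and the remedy need not disturb it.

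A reader might infer that the rule forbids emergency referral or removes the APP's urgent visit and ED decision. The document supports neither. Referral is left unlisted, and the APP's steps depend on whether the AF with RVR event is communicated. Nor would a tally of lost steps be meaningful, because the emergency room is one side of an either-or choice.

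**Conclusion.** The point holds and is worth fixing before phase 3. In three of the five pairings that contain AF with RVR, the pathway selected by the rule does not list the nurse's emergency room option. In two of those three, it also replaces a direct call with a note, unless the diuretic dose is already escalated. In all three, the APP's urgent steps are possible but not assured.

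This rests on reading the rule as choosing one pathway, as its worked example does, and on the article's text without Figure 6 or the structured note. The pairing count describes the written workflow. It does not measure how often the pairings occur or how much risk they carry, and the article shows no harm.

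**What to change.** Keep the ranking. Add one sentence to Workflow and Clinical Management after the ranking, and carry it into Figure 6 and the structured note:

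> Whenever AF with RVR is among the active alerts, its steps (HHN call to the APP or HF specialist, or emergency room referral; APP platform review, urgent telephone or video visit, and ED-or-home decision) are carried out in addition to those of any higher-ranked alert.

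Moving AF with RVR up the ranking would be a poorer remedy. Under the same one-pathway rule, it would drop the home IV diuresis assessment (yellow zone, weight gain) or the laboratory tests (MCI). The additive sentence keeps both.

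Phase 2 is intended for adjusting alerts and workflows, so the change belongs there, before the workflow is fixed for phase 3. If phase 3 is already enrolling, it should be made at once. The cost is a wording change, brief retraining, and possibly a few more urgent visits or ED referrals. It needs no additional patients or data collection.

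### When atrial fibrillation with rapid ventricular response coincides with yellow zone symptoms, weight gain or an MCI alert, the pathway followed omits the nurse's emergency-room option (3 pairings) and direct provider call (2 pairings)

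*Protocol article*

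**What the plan says.** All of this is in the protocol article, Methods, Workflow and Clinical Management.

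- **Rule for several alerts** (text after Figure 6): "If a patient has >1 alert, the pathway for the alert deemed more severe will be followed".
- **Ranking:** red zone symptoms first, yellow zone symptoms second, then "weight gain of ≥5 lb (≥2.3 kg), an MCI alert, an atrial fibrillation with rapid ventricular response alert, and a tachypnea or tachycardia alert".
- **Worked example:** "if the patient has a new red zone symptom and an MCI alert, the pathway for the red zone alert will be followed".
- **AF with RVR, nurse's step:** after phoning the patient and completing the note, the nurse is to "call the APP or HF specialist, and route the note to the APP pool and HF specialist, or send the patient to the emergency room".
- **AF with RVR, APP's steps:** these begin with a condition, "If the APP is alerted to an atrial fibrillation with rapid ventricular response event, they will review the vendor platform to assess the event". An urgent remote visit comes next, followed by a choice of setting, where the article says "The APP will determine whether the patient needs to be sent to the ED or whether the patient can be safely managed at home"; finally the plan is talked through with the attending.
- **Yellow zone:** the nurse phones the patient and completes the note, which goes to the APP pool and the patient's HF specialist. The APP arranges a telephone visit and considers home intravenous diuresis.
- **Weight gain:** the nurse phones the patient and routes the note to the APPs and the attending physician. The APP arranges a telephone visit and considers home intravenous diuresis.
- **MCI (multivariate change index):** the nurse phones the patient, phones the APP and routes the note. The APP arranges a telephone visit and may choose diuretic escalation, an urgent clinic visit or alerting the attending.

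**The concern.** The ranking decides which set of instructions the nurse works from, so it should not place an alert with an urgent response below alerts with milder ones. Here it does. Of the six ranked alerts, only red zone symptoms and AF with RVR let the nurse send the patient to emergency care. Yet AF with RVR gives way to three alerts whose pathways contain no such step.

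A patient with AF with RVR alone gets a direct call to a provider or an emergency-room referral. If the same patient has also gained 5 lb, the pathway followed is, as written, a routed note. What is at stake is patient safety: a possible delay in assessing the arrhythmia. It does not touch any endpoint, comparison or analysis.

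**Working it through.** The document gives no figure to reproduce. The check is a count from the written pathways.

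**Step 1. Pairings.** There are six ranked alert classes, so AF with RVR can coincide with 6 − 1 = 5 others. It ranks fifth, so four outrank it. It outranks tachypnea or tachycardia, and in that pairing its own pathway is followed.

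**Step 2. Nurse's options in each pathway.**

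| Pathway followed | Emergency referral by nurse | Direct call to a provider | Note to APP and APP telephone visit |
|---|---|---|---|
| AF with RVR alone (reference) | yes | yes (APP or HF specialist) | note yes; visit urgent, by telephone or video |
| Red zone | yes | yes (HF specialist) | not needed for the comparison |
| Yellow zone | no | no | yes |
| Weight gain | no | no | yes |
| MCI | no | yes (APP) | yes |

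**Step 3. Counts.**

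- Red zone keeps both options, so affected pairings = 4 − 1 = 3.
- Emergency-room option absent: yellow zone, weight gain, MCI = 3 of 3.
- Direct provider call absent: yellow zone, weight gain = 2 of 3.
- In the AF with RVR pathway the call and the referral are alternatives, so the two counts should not be added.

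**Step 4. APP's steps.** Four steps depend on the APP being alerted to the AF event: platform review, urgent visit, decision between emergency department and home, and discussion with the attending. They are not lost in the three pairings. They follow only if the note or call carries the AF event, and none of the three pathways requires that. They are conditional in 3 of 3.

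**Step 5. Exception.** For a patient already on an escalated diuretic dose, the text after Figure 6 has the nurse phone the APP or HF specialist for any event notification. This restores the call in the two pairings, but not the emergency-room option.

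**Step 6. After the fix.** If the AF with RVR call or referral is added to the higher-ranked pathway, 0 of 3 pairings lack the emergency-room option and 0 of 3 lack the direct call.

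**The case against.** The counts are not in dispute. The case against rests on what the text does not say and on what remains in place.

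1. *The rule does not say that only the higher-ranked pathway is followed.* True. But the worked example names just that pathway, and nothing tells the nurse to combine pathways.
2. *Figure 6 and the structured note are not shown.* The Discussion says the note generates recommendations from what the nurse enters, so an AF entry might trigger escalation whatever else is present. This stands as a real limit. The figure is less likely to help, because the text says it uses the same order of severity.
3. *Safeguards remain.* New or worsening red zone symptoms, which include chest pain and breathlessness at rest, outrank everything, so the affected pairings are those without them. The nurse phones the patient in all three pathways, and the APP gets the note and holds a telephone visit. Device and Notification Mechanisms ties APP and specialist notification to acuity and event type. All of this stands and limits the possible harm, but none of it gives the nurse an emergency-room step.
4. *The MCI pairing is thin.* Fair: the APP is still phoned and can arrange an urgent clinic visit. Only the nurse's own emergency-room alternative is missing.
5. *The timescale is a daily one.* The nurse reviews the portal daily, and response is measured within 24 hours, so call versus note may matter little. The size of any delay is indeed unknown. Equally, a note in place of a call comes on top of the daily review interval.
6. *Clinical judgment covers the gap.* The protocol leaves judgment to the provider once the nurse has escalated, whereas this gap is at the nurse's step. The phase 1 results also report that missing recommendations for alerts other than MCI made it hard to know what to do.

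**Conclusion.** The concern holds. The article states a rule and a complete ranking which, set against its own pathways, give a weaker written first response to AF with RVR when one of three other alerts is also present. Of the 5 pairings involving AF with RVR, 3 are affected. The nurse's emergency-room option is absent in all 3. The direct call is absent in 2, except for patients already on an escalated diuretic dose. The four APP steps become conditional in all 3.

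This assumes that the nurse follows the higher-ranked pathway alone, as the worked example suggests, and that the unseen figure and note do not already deal with a coexisting AF event. The text gives no data on co-occurrence and no response time for an urgent or an ordinary telephone visit, so neither the frequency nor the length of any delay can be estimated. It is worth correcting before phase 3 on safety grounds.

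**What to change.** Keep the rule and ranking, and add two sentences after the rule "If a patient has >1 alert, the pathway for the alert deemed more severe will be followed". Proposed text:

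> Where AF with RVR is one of the alerts, the home health nurse, besides following the higher-ranked pathway, phones the APP or HF specialist about the AF with RVR event or refers the patient to the emergency room. The APP steps for AF with RVR then apply whatever other alerts are present.

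This is better than moving AF with RVR up the list, which would displace the home intravenous diuresis assessment in the yellow zone and weight gain pathways. The clinical leads should confirm the choice. If Figure 6 or the structured note already handles the combination, the text need only say so.

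The cost is two sentences, matching changes to Figure 6 and the structured note, a protocol amendment with ethics review, and possibly a few more urgent contacts (number unknown). The wording uses only roles and steps that the AF with RVR pathway already assigns. Phase 2 is the stated period for adjusting alerts and workflows, so the change can be made before the 45 phase 3 patients are enrolled.
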